#### Primary hypotheses

High compared with low frequency treatment will normalize brain structure and function.

##### Brain structure

Based on prior findings in chronic depression patients in an RCT of medication therapy vs placebo [81], changes in cortical thickness, representing therapy-induced, neuroplastic compensatory changes in brain structure, will normalize during 1 year of treatment – i.e., baseline abnormalities relative to healthy control values will change more during high frequency treatment compared with low frequency treatment, and 1 year after beginning treatment will be statistically indistinguishable from healthy control values. Change in cortical thickness will correlate significantly with the magnitude of clinical improvement after 1 year of treatment.

##### Brain activation

High compared with low frequency treatment will produce greater change in brain activity (a greater degree of normalization relative to healthy control values) in ventral medial brain regions during the functional MRI (fMRI) Cyberball paradigm for social exclusion, and the changes in brain activity will significantly mediate clinical improvement during the 1-year duration of treatment.

##### Functional connectivity

High compared with low frequency treatment will produce a greater change in measures of functional brain connectivity after 1 year of treatment during resting state fMRI, particularly in the default mode network (DMN), which likely subserves the capacity for free association. Based on prior findings in chronically depressed patients in an RCT of medication therapy vs placebo [82], we expect high compared with low frequency treatment to produce a greater degree of normalization in DMN activity relative to activity in healthy control participants.

##### Tissue microstructure

High compared with low frequency treatment will produce a more pronounced normalization of indices of tissue microstructure in white matter (increasing fractional anisotropy and decreasing mean diffusivity) measured with diffusion tensor imaging (DTI).

#### Secondary hypotheses

##### Psychopathology

Although high and low frequency treatments will both produce clinical improvement, improvement will be significantly greater for high frequency treatment in structural integration (measured with the Operationalized Psychodynamic Diagnosis Structure Questionnaire (OPD-SQ)), depressive symptoms (measured with the BDI-2), and in the manifest dreams (measured with DREams Assessment Scale for measuring Changes in manifest dream (DREAMS-C). Improvement in these clinical measures will associate significantly with the regional changes in MRI measures that change in response to high vs low frequency treatment.

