## Methods/Design

### Study design

MODE is a randomized, parallel, superiority and single blinded controlled trial comparing the effectiveness of two active interventions – high frequency (*n* = 30) vs low frequency (*n* = 30) psychoanalyses – in modifying brain structure and function over one year of treatment chronic depression patients who have a history of early life trauma (Fig. 1).

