### Intervention and comparator

Study intervention will be comprised of low frequency psychoanalytic psychotherapy (1 session a week) for early traumatized, chronically depressed patients and high frequency psychoanalytic psychotherapy (3–4 weekly sessions). The active comparator condition, low frequency psychoanalysis, delivered by study therapists who are experts in delivering both frequencies, and with the same overall manual based theoretical framework and technical interventions [86], will ensure that they will be equally aligned to both high and low frequency therapies. A group of healthy controls will be needed for brain imaging comparison purposes. A control group will allow to measure cortical thickness in patients with chronic depression in comparison to healthy control participants. Therapy sessions (45–50’ each) will be delivered in the private practice rooms or rooms of the outpatient clinics of the local psychotherapeutic institutions. Patients who will require a combination therapy of medication and psychotherapy during treatment will not be excluded but form a special subgroup that will be treated separately during data analyses. Patients who will require a change in psychotherapy setting during treatment according to patient and therapist decision will be analyzed as randomized. MODE study duration will be one year, but after 1 year of treatment initiation, treatment may continue according to patient and therapist decision. Treatments will be financed in the usual way in the participating countries (in Germany by the health insurance companies, in the US and Switzerland partly by the health insurance companies, partly by the patients themselves).

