### Outcome measures

Study participants will be assessed as detailed below and in Table 3, for primary and secondary outcome measures. Patients will be assessed by independent and trained clinicians who are blind to treatment conditions.

**Table 3 Tab3:** Study timetable of assessments

Assessments	Screening	Visit 1	Visit 2	Visit 3	Visit 4	Visit 5
*Description*	*Inclusion*	*Study start*	*FU 3 months*	*FU 6 months*	*FU 9 months*	*Study end*
*Days*	*Day -x*	*Day 0*	*Day 91*	*Day 182*	*Day 273*	*Day 365*
*Window (dates)*			± *7*	± *7*	± *7*	± *3*
*Weeks*		*0*	*13*	*26*	*39*	*52*
Informed consent signed	X					
Eligibility	X					
Demographics		X				
SCID (CI)	X	(X)^a^				X
Psychoanalytic interview	X	(X)^a^				
MRI scan	X	(X)^a^				X
Trust game	X	(X)^a^				X
GAF (Cl)		X				X
BDI-II (SR)	X	X	X	X	X	X
DEQ (SR)		X	X	X	X	X
QIDS (Cl, SR)		X	X (only SR)	X (only SR)	X (only SR)	X
SCL-90-R (SR)		X	X	X	X	X
CTQ (SR)	X					
IIP (SR)		X	X	X	X	X
Work Ability Index (SR)		X	X	X	X	X
OPD_SF (SR)		X	X	X	X	X
Dream Diary (SR)						X
Patient trauma narratives		X				X
WAI-SRp (SR)		Collected each month from Assessment 1 to 5				
Psychotherapy		Throughout study				
Adverse Events			X	X	X	X
SAE		Throughout study				
Medication		X	X	X	X	X

*FU* Follow-up, *Cl* Clinician rated, *SR* Self-reported, *SCID* Structured Clinical Interview for DSM, *GAF* Global Assessment of functioning, *BDI-II* Beck Depression Inventory-II, *DEQ* Depressive Experience Questionnaire, *QIDS* Quick Inventory of Depressive Symptoms (Cl, SR), *SCL-90-R* Symptom Checklist, *CTQ* Childhood Trauma Questionnaire, *IIP* Inventory Interpersonal Problems, *WAI* Work Ability Index, *OPD-SF* OPD structure questionnaire, *WAI-SRp* Working Alliance Inventory, *SAE* Severe Adverse Event

^a^Depending on the availability of the persons concerned, the first MRI examination, the administration of the Trustgame, the SCID interview, and the psychoanalytical interview can take place at the screening visit or visit 1

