#### Secondary outcome measures

MODE will investigate whether and how brain changes are associated with common measures of change for patients with chronic depression and early trauma after one year of treatment. To achieve this aim and as recommended in meta-analytic reviews, various broad areas of patient’s functioning are assessed including (1) psychopathology, (2) personality, social and work functioning, and (3) dynamic functioning which may underlie impaired functioning and contribute to vulnerability to psychiatric disorders [94]. Due to their depressive symptomatology, patients may face some difficulties with self-report questionnaires. Therefore, we have restricted the total number of items included in the assessment battery (Table 8).

**Table 8 Tab8:** Secondary outcomes: clinical response measures

Clinical therapeutic outcomes	Clinical-psychoanalytical outcomes
• Beck Depression Inventory (BDI)	• Operationalized Psychodynamic Diagnostics self-report questionnaire (OPD-SQ)
• Depressive Experience Questionnaire (DEQ)	• The Social Cognition and Object Relations Scale-Global Rating Method (SCORS-G)
• Social Functioning Global Assessment of Functioning (GAF)	• Reports of trauma memories (Pennebaker)
• Work Ability Index (WAI)	
• Therapeutic alliance Working Alliance Inventory (WAI-SRp)	
• Inventory of Interpersonal Problems (IIP)	

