###### Depression

Depressive symptoms will be assessed using three instruments: (1) The Inventory of Depressive Symptom (QIDS; [96]), a clinician rating measure (QIDS-C_16_); (2) the self-rated version of the QIDS (QIDS-SR_16_), 16-item measures of depressive symptoms; and (3) the Berg -Depression Inventory (BDI-II; [97]). The Depressive Experience Questionnaire (DEQ; [98]), which assesses a wide range of life experiences often reported by depressed individuals but not considered symptoms of depression.

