### Blinding

All the members of the investigating team (SCID /LIFE interviewers, MRI team etc.) will be blinded (they do neither know the treatment arm nor the names of the study therapists).

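### The depression hypothesis is tied to the self-reported BDI-2 alone, although a blinded clinician-rated QIDS is collected at the same two key visits and is missing from that hypothesis and from Table 8

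*Protocol article*

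**What the plan says.** All references are to the protocol article.

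- **Secondary hypotheses, Psychopathology.** Superiority of high frequency treatment is predicted for structural integration (an OPD questionnaire), for "depressive symptoms (measured with the BDI-2") and for manifest dreams. Improvement on these measures is also expected to associate with the regional MRI changes. No other depression scale is named.
- **Outcome measures, Table 3.** The BDI-II is marked self-reported and is taken at screening and at all five visits. The QIDS is marked clinician-rated and self-rated at Visit 1 (Day 0) and Visit 5 (Day 365), and self-rated only at the three visits between. The same section states: "Patients will be assessed by independent and trained clinicians who are blind to treatment conditions".
- **Blinding and Study design.** "All the members of the investigating team (SCID /LIFE interviewers, MRI team etc.) will be blinded", and the trial is described as a "randomized, parallel, superiority and single blinded controlled trial".
- **Intervention and comparator.** The arms are "low frequency psychoanalytic psychotherapy (1 session a week") and "high frequency psychoanalytic psychotherapy (3–4 weekly sessions").
- **Depression (under Secondary outcome measures).** Three instruments are listed. The QIDS-C comes first, as "a clinician rating measure", followed by the QIDS-SR and the BDI-II.
- **Table 8, "Secondary outcomes: clinical response measures".** It lists the BDI but no version of the QIDS.

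**The concern.** A patient who attends 3–4 sessions a week knows it, and so does one who attends once. Patients may expect more from the more intensive treatment and report accordingly. The design addresses therapist allegiance by using therapists expert in both frequencies and a common manual, but that does not deal with what patients expect. A between-arm difference on a self-rated scale therefore mixes any treatment effect with any reporting effect.

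The trial already plans a depression rating less exposed to this problem, at the same baseline and 1-year time points as the MRI comparison. Leaving it out of the hypothesis has two consequences. A claim of greater improvement in depression could rest on self-report alone. The stated association between clinical improvement and brain change would also use only the self-rated scale for depression. Because the text lists the QIDS-C as a secondary instrument and Table 8 does not, a reader of the results could not tell what weight it was meant to carry.

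**Working it through.** **1. The passages side by side**

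| Place | BDI-II | QIDS-C |
|---|---|---|
| Secondary hypothesis, Psychopathology | named | not named |
| Table 8 | listed | not listed |
| Depression section | third of three | first of three |
| Table 3 | self-rated, screening and Visits 1–5 | clinician-rated, Visits 1 and 5 |
| Rater blind to arm | no (inferred) | yes (stated for the clinicians) |

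No sentence says that patients are unblinded. This follows from the 1 versus 3–4 weekly sessions and fits the single-blind label.

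**2. The two sources are not interchangeable.** The Introduction reports 3-year full remission in the LAC study as 45% self-rated (BDI ≤ 12) and 61% clinician-rated (QIDS-C ≤ 5). Scales and cut-offs differ, so the 16-point gap is no measure of bias. It does show that the choice of source can change the result, and that the predecessor study reported both.

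**3. What an expectancy shift would do.** The plan gives no figure to reproduce here. Inputs: 30 per arm (Study design); two-sided α = 0.05 (assumed for this secondary comparison); no true effect; a reporting shift of b SD towards high frequency (assumed).

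Standard error of the difference in SD units = √(2/30) = 0.258. Noncentrality = b / 0.258. Two-sample t-test, 58 degrees of freedom:

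| b (SD, assumed) | Noncentrality | Chance of p < 0.05 |
|---|---|---|
| 0 | 0 | 5% |
| 0.2 | 0.77 | 11.9% |
| 0.3 | 1.16 | 20.8% |
| 0.4 | 1.55 | 33.2% |

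**4. Would a same-direction rule be enough?** Suppose a BDI-II claim were allowed only if the QIDS-C estimate pointed the same way. Take the case most favourable to that rule: no true effect, a QIDS-C free of bias, and an assumed correlation of 0.5 to 0.8 between the two estimates. The claim rate is the bivariate normal probability that the BDI-II statistic exceeds 1.96 and the QIDS-C statistic exceeds 0, with means b/0.258 and 0.

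- b = 0.3: about 21% without the rule, 16% to 20% with it.
- b = 0.2: about 12% without the rule, 10% to 12% with it.

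If the QIDS-C carries half the bias, the 0.3 SD figure stays at about 20% to 21%. The rule leaves most of the error in place.

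**5. Precision of the blinded estimate.** Before baseline adjustment, the half-width of a 95% confidence interval with 30 per arm is 2.00 × 0.258 = 0.52 SD. The QIDS-C estimate must be read with its interval, and a non-significant result would not show that the arms are equal.

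**The case against.** The strongest reply is that the QIDS-C does have a place in the plan. The Depression section, under the heading for secondary outcomes, names it first, and Table 3 schedules it. Table 8 is plainly not exhaustive: it also omits the SCL-90-R and the Trust game, which are described under the same heading. How a secondary scale is modelled may properly be left to an analysis plan that is not shown. All of this stands. A reader might infer that the protocol drops the blinded rating or gives it no role, and the documents do not support that.

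Nor can it be said that every measure in the hypothesis is completed by unblinded patients. Patients write the dream diaries, but the content is then assessed with rating and word-count methods. Table 8 also includes the clinician-rated GAF, so a blinded clinical rating is listed, although it concerns functioning and not depression.

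The reach is limited too. The primary outcomes are MRI measures. The primary hypotheses and Aim 2 refer to clinical improvement without naming a scale, so the self-report link to brain change is established only for the association stated in the psychopathology hypothesis. Finally, the size of any expectancy effect is unknown, and a clinician rating still draws partly on what the patient says.

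What the reply does not remove: the article itself fixes the BDI-2 as the sole depression measure in a superiority hypothesis, and its outcome table does not match its instrument text. Those are statements in this document, not details left for later.

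**Conclusion.** The point holds in a limited form. The hypothesis on depressive symptoms, and its association with brain change, uses only a self-reported scale in patients who know their session frequency. A clinician rating by assessors stated to be blind, scheduled at Day 0 and Day 365 and named as a secondary instrument, is missing from that hypothesis and from Table 8.

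This is a cheap improvement to a secondary hypothesis and does not threaten the primary imaging analysis. The 12% to 33% false-positive range illustrates assumed shifts of 0.2 to 0.4 SD; it is not an estimate of what will happen in this trial. The conclusion does not depend on it. It rests on the cross-reading and on the inference that patients know their arm.

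**What to change.** 1. Add the QIDS-C to Table 8, and to the psychopathology hypothesis as the blinded measure of depressive symptoms, beside the BDI-II. Keep the five-visit BDI-II as it is.
2. Analyse the QIDS-C at 1 year, adjusted for its baseline value, and report both between-arm estimates with 95% confidence intervals.
3. Repeat the association between brain change and clinical improvement with the QIDS-C.
4. State in advance how the two results will be read together. A difference on the BDI-II that the QIDS-C estimate and its interval do not support is described as a self-report finding that expectancy could explain. Do not rely on agreement in direction alone, for the reason shown in the working.

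**Cost.** Rewording, and one additional between-arm model plus the repeated association, on data already scheduled. The drawbacks are one more secondary test, only two QIDS-C time points, and a rating that reduces expectancy bias without removing it.

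The questionnaire called OPD-SQ in the hypothesis and Table 8 is called OPD-SF in Table 3 and in the section on psychodynamic functioning. That is a separate clerical matter, which can be settled in the same edit.

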##### Metabolic profile (only for a subgroup in Frankfurt)

Proton MR Spectroscopy (^1^H-MRS) measures brain metabolites N-acetyl-aspartate (NAA), choline (Cho) and creatine (Cr) as potential in vivo biomarker of the integrity of neurons (NAA), membranes (Cho) and glia (Cr) [83, 84]. High compared with low frequency treatment will produce a more pronounced changes of metabolite concentration in N-Acetylaspartate (NAA/Cr, respectively), indicating normalization of neuronal integrity measured with MR spectroscopy (^1^H MRS). Change in NAA (NAA/Cr) will correlate significantly with the magnitude of clinical improvement after 1 year of treatment.

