###### MRI Scanning MR spectroscopy (1H MRS)

Scans are acquired on 3.0 T scanners, Siemens Prisma in Frankfurt subgroup only. Spectroscopy was performed at the end of the MRI examination. An axial slice was recorded with 2D MRSI using an acquisition weighted circular phase encoding scheme on a 20 × 20 matrix, FOV of 240 × 240 mm^2^, 12 mm slice thickness, nominal voxel size of 12 × 12x12 mm^3^, TR 2000 ms, TE 40 ms, and 2 acquisitions. The volume of interest (VOI), which was selected by using the sLASER sequence from the vendor and outer volume suppression, was adjusted to contain GM and WM. Spectra were analyzed using LCModel [116]. The basis data set contained simulated spectra from Alanine, Creatine, GABA, Glucose, Glutamine, Glutamate, Glycine, Choline, Glutathion, Lactate, Mio-Inositol, N-acetyl-aspapartate-glutamate and N-Acetyl-Aspapartate.

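### The spectroscopy hypothesis treats NAA and NAA/Cr as interchangeable and reads a change in either as neuronal, although the plan itself describes Cr as a potential glial marker

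*Protocol article*

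**What the plan says.** The section on the metabolic profile, under the secondary hypotheses, introduces the three metabolites as "potential in vivo biomarker of the integrity of neurons (NAA), membranes (Cho) and glia (Cr"). The next sentence predicts larger changes under high than under low frequency treatment in "metabolite concentration in N-Acetylaspartate (NAA/Cr, respectively), indicating normalization of neuronal integrity". The section ends with a second prediction: "Change in NAA (NAA/Cr) will correlate significantly with the magnitude of clinical improvement after 1 year of treatment". Both predictions name NAA with NAA/Cr in brackets, and neither says which of the two settles the hypothesis.

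The section on MR spectroscopy scanning describes the acquisition: "An axial slice was recorded with 2D MRSI using an acquisition weighted circular phase encoding scheme on a 20 × 20 matrix", with "12 mm slice thickness, nominal voxel size of 12 × 12x12 mm^3". The volume of interest "was adjusted to contain GM and WM". On processing it says "Spectra were analyzed using LCModel", with creatine and NAA listed as separate components of the basis set.

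In the brain structure hypothesis, the article expects cortical thickness to change more under high than under low frequency treatment, and expects that change to correlate with clinical improvement.

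**The concern.** A ratio moves when either of its parts moves. If the denominator is a potential marker of glia, as the article says, then a change in the ratio does not by itself locate the change in neurons. The article nevertheless attaches one interpretation, restored neuronal integrity, to NAA and NAA/Cr alike. If the two disagree, either could be presented as confirming the hypothesis.

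What is at stake is a mechanistic statement. The article presents the trial as a search for brain mechanisms and mediators of treatment response. A conclusion that more frequent treatment restores neuronal integrity, or that such restoration tracks clinical improvement, could rest on a shift in creatine. Conversely, a true gain in NAA accompanied by a rise in Cr could be missed if the ratio is taken as the deciding measure.

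A smaller, related point is tissue composition. The volume of interest holds both grey and white matter, and the article's own primary hypothesis expects cortical change to differ by arm. If it does, the tissue mix in the measured volume might differ by arm as well.

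**Working it through.** **Reproducing the plan's own figure.** The only checkable number here is the in-plane voxel size. Field of view 240 mm divided by 20 matrix steps = 12 mm, as stated. No sample size, effect size or power is given for spectroscopy, so there is none to check.

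**Definitions side by side.** The article links NAA to neurons and Cr to glia. NAA/Cr is then a neuron-to-glia ratio. The stated reading of a change is neuronal only. The two agree if Cr is stable, which the article does not state.

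**Ratio arithmetic.** Let NAA change by a fraction a and Cr by a fraction c. The relative change in NAA/Cr is (1 + a)/(1 + c) - 1. The values of c are illustrative.

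| NAA change (a) | Cr change (c) | Calculation | Change in NAA/Cr |
|---|---|---|---|
| 0 | -3% | 1/0.97 - 1 | +3.1% |
| 0 | -5% | 1/0.95 - 1 | +5.3% |
| 0 | -10% | 1/0.90 - 1 | +11.1% |
| 0 | +3% | 1/1.03 - 1 | -2.9% |
| 0 | +5% | 1/1.05 - 1 | -4.8% |
| 0 | +10% | 1/1.10 - 1 | -9.1% |
| +5% | +5% | 1.05/1.05 - 1 | 0 |

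In the first six rows the ratio moves with no change in NAA. In the last row a 5% gain in NAA disappears from the ratio.

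**Tissue mix (all inputs assumed; none is in the documents).** Set NAA and Cr in grey matter to 1. In white matter let Cr = w and NAA = w × k, with w from 0.7 to 0.9 and k, the white-to-grey ratio of NAA/Cr, from 1.1 to 1.5. For grey-matter fraction f:

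- Cr(f) = f + (1 - f)w
- NAA(f) = f + (1 - f)wk

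Move f from 0.50 to 0.55. Worked case with w = 0.8 and k = 1.3:

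- Cr goes from 0.900 to 0.910.
- NAA goes from 1.020 to 1.018, a change of -0.2%.
- NAA/Cr goes from 1.133 to 1.119, a change of -1.3%.

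Over the whole grid, NAA/Cr moves by -0.5% to -2.0% and NAA alone by -1.5% to +1.3%. Under these assumptions the tissue effect is smaller than the Cr effects tabulated above. It also touches NAA as well as the ratio, so choosing NAA does not remove it.

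**The case against.** The strongest reply is that NAA is named first and the ratio only in brackets, and that the spectral fit yields NAA and Cr separately. A change driven by Cr alone would then show as a moving ratio with a flat NAA, and a careful analyst would see it. This stands in part. A reader might infer that NAA/Cr is the sole endpoint and that a creatine change would inevitably be reported as neuronal. The text does not support that; it supports only that such a change could be so reported, because the deciding measure is not fixed and both measures carry the same interpretation.

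Three other stronger readings also fail:

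- Cr as an outcome in its own right, or as a quantity expected to change. It appears only in a background sentence as a potential biomarker, with no hypothesis of its own.
- Measurement in one voxel of mixed tissue. The acquisition is a multi-voxel slice, and it is the volume of interest that contains both tissues.
- The absence of a tissue correction as an error. A condensed article commonly leaves such processing detail to the full protocol or analysis plan, which are not shown. The article also gives neither the slice position nor the size of the expected cortical change. Tissue change unrelated to arm would add noise and would not bias the randomised comparison.

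It is also fair to say that the ratio has a purpose: scanner scaling cancels in it. Preferring NAA over NAA/Cr is a trade-off.

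**Conclusion.** The point holds in a limited form. Within one section the article describes Cr as a potential glial marker, places it in the denominator of a measure used interchangeably with NAA, and reads a change in either as neuronal. That inference is stated in the text and the ratio cannot carry it alone, so the point does not depend on anything the article omits.

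On size: a Cr change of a few percent moves the ratio by about the same percentage in the opposite direction, for example -5% giving +5.3%. How far Cr will actually move in this trial is unknown, so these figures show sensitivity and do not predict a bias. The tissue-mix figures rest wholly on assumed inputs and are a secondary consideration.

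Severity is minor. Spectroscopy is not among the primary outcomes, the modalities in the power calculation or the dependent variables named for the primary hypotheses. No primary conclusion depends on it.

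**What to change.** - State which measure, NAA or NAA/Cr, decides the spectroscopy hypothesis and its correlation with clinical improvement.
- Analyse NAA and Cr separately from the existing LCModel fit, with the same treatment-by-time model. Report the estimate and confidence interval for each.
- Do not make the neuronal reading conditional on a non-significant difference in Cr. In a single-site subgroup of unstated size, non-significance is weak evidence that Cr is equal between arms.
- Limit the neuronal-integrity wording, including for the clinical correlation, to changes carried by NAA. Otherwise claim only a change in the NAA/Cr ratio. The same restriction applies if the data hold no usable scaling for NAA other than Cr, which the article does not show either way.
- As a secondary sensitivity check, adjust for the grey/white fraction of the measured volume at each visit, taken from the anatomical MRI of the same session. Keep it a sensitivity check: if treatment itself changes tissue fraction, the adjusted comparison answers a different question.

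The cost is a few sentences, a rerun of models on existing fits and segmentation of anatomical scans that the protocol already schedules. The downside is that NAA without the Cr ratio is somewhat noisier, because scaling variation no longer cancels.
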